### Interim analyses {21b}

The intervention in eliPfad consists of several tried and tested procedures, such as regular measurement of vital signs using certified equipment, as well as home physiotherapy exercises. None of these procedures pose a substantial risk to the patient, so there is no indication to carry out interim analyses that could lead to an early stop of the study due to an obvious harm to the patient.

Furthermore, the study is not an adaptive trial in which the sample size might be adjusted after interim analyses.

For these reasons, no interim analyses are planned.

### Methods for additional analyses (e.g., subgroup analyses) {20b}

#### Analyses of safety-related aspects

Adverse events are assessed by relation, severity, and intensity; treatment comparisons are made in categories (e.g., MedDRA codes).

Changes in laboratory values are shown using shift tables; in addition, individual time courses are described and extreme values are marked in lists.

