## Trial design {8}

eliPfad is a pragmatic, randomized, controlled, open-label, multicenter trial with one intervention and one control group. The allocation ratio is 1:1. eliPfad is a superiority trial in which the superiority of the new model of care to the current standard of care is to be proven.

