**Clinical data collection**					
Evaluation of adverse events (AE)		X	X	X	X
Duration index hospital stay			X		
Duration stays in different wards			X		
Transfer to external hospitals			X		
Transfer to rehabilitation facilities			X		
MPI (geriatric assessment)	X		X	X	X
Health literacy		X	X	X	X
Quality of life/depression/health status/self-efficacy		X	X	X	X
Medication plan		X	X	X	X
Minimal Nutritional Assessment		X	X	X	X
Mobility tests		X	X	X	X
Patient orientation		X		X	X
Personal goals/self-management/personal therapy burden			X	X	X
Photo documentation drugs				X	X
Number of rehospitalizations				X	X
Health economic evaluation					X
Utilization of rehabilitation services					X
Length of stay in inpatient facilities					X
Death					X

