### Adverse event reporting and harms {22}

No adverse events (AEs) in the strict sense are expected to be caused by the intervention. However, due to pre-existing (chronic) diseases, numerous complications are possible. In addition, the participants’ underlying diseases may worsen. These complications are not documented separately.

No novel or unapproved methods will be used as part of the intervention. Conceivably, a safety-related event could occur during independent home exercise; for example, a fall during a mobilization exercise. Events such as these and all other events that are not associated with the natural course of the pre-existing (chronic) diseases are documented as an AE. In case that such an event leads to hospitalization or death of the patient, it will be recorded as an SAE. AEs and SAEs will be recorded in the electronic data capture system (secuTrial® database) by the study team. AEs and SAEs will be identified by the study team during the weekly video calls between the case manager and the patient or during the assessments. SAEs will be immediately reported to the sponsor by the study teams.

Due to the open-label character of the trial, the obligation to document safety-related events begins in the intervention group at the time of enrollment and ends after the 6-week outpatient phase following the index inpatient stay at T2. There is no documentation requirement in the control group.

An overview of safety-relevant events will be provided to the ethics committee upon request after completion of the study.

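### Adverse events are to be compared between arms, but their documentation is required only in the intervention arm and only until T2

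*Protocol article*

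**What the plan says.** Three places in the protocol article govern adverse events.

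- **Methods for additional analyses {20b}, Analyses of safety-related aspects:** "Adverse events are assessed by relation, severity, and intensity; treatment comparisons are made in categories (e.g., MedDRA codes". Under Trial design {8} there is one intervention and one control group ("The allocation ratio is 1:1"), so a treatment comparison can only mean eliPfad against standard care.
- **Adverse event reporting and harms {22}:** "the obligation to document safety-related events begins in the intervention group at the time of enrollment and ends after the 6-week outpatient phase", that is, until T2, 42 days after discharge. For the other arm: "There is no documentation requirement in the control group". Events are found "during the weekly video calls between the case manager and the patient or during the assessments". Complications or worsening of the underlying diseases are not documented separately, whereas "all other events that are not associated with the natural course of the pre-existing (chronic) diseases are documented as an AE".
- **Participant timeline {13}, Table 1:** the row labelled "Evaluation of adverse events (AE" is marked at T0, T1, T2 and T3, without distinction by arm.

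**The concern.** A between-arm comparison of adverse events needs events counted in both arms by the same definition, over the same period and with the same effort to find them. The harms section provides this for one arm only. A comparison built on such data mixes any real effect of eliPfad with the difference in recording, and the difference in recording points towards apparent harm from eliPfad.

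The section itself names a fall during independent home exercise as a conceivable event. Falls also occur in frail patients under standard care, so a count in the intervention arm alone cannot show whether the programme adds any. The article proposes eliPfad as a possible new standard of care, so a misleading safety table would matter.

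This is not detail that can be left to the SAP. A SAP can choose how events are compared, but it cannot recover control-arm events that were never collected.

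**Working it through.** **1. The sections side by side**

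| Item | Intervention arm | Control arm |
|---|---|---|
| AE comparison ({20b}) | planned | planned |
| Duty to document ({22}) | enrolment to T2 | none |
| Detection by weekly video call ({11a}, {22}) | yes | no, the calls are part of the intervention |
| Detection at assessments ({12}, {22}) | yes | visits take place, no duty to record |
| AE row in Table 1 | T0 to T3 | T0 to T3 (no distinction by arm) |

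The first row cannot be carried out validly from data collected under the second and third. The last row conflicts with the second on both the arms covered and the end of collection.

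**2. The T2/T3 conflict**

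T2 is 42 days and T3 is 180 days after discharge (Outcomes {12}). The period that Table 1 covers and the harms section excludes is 180 − 42 = 138 days, or 138/180 = 77% of post-discharge follow-up. All of it falls after the intervention ends at six weeks.

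**3. Direction and possible size of the bias**

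The article gives no AE rate, so there is no figure to reproduce and no size to state. The following only shows how the bias behaves under assumed values: the same true AE risk *r* in both arms, full recording in the intervention arm, a share *s* of events recorded in controls, and *n* = 474 per arm (Sample size {14}).

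- Recorded risks: p1 = r and p0 = r·s. The recorded risk ratio is p1/p0 = 1/s, although the true ratio is 1.
- Approximate chance that a two-sided 5% test shows a false excess with eliPfad, with p̄ = (p1 + p0)/2:
 Φ{[p1 − p0 − 1.96·√(2p̄(1−p̄)/n)] / √([p1(1−p1) + p0(1−p0)]/n)}.
- Example, r = 5% and s = 0.5: p1 − p0 = 0.025 and p̄ = 0.0375. The null term is 1.96 × 0.01234 = 0.02419, and the other standard error is 0.01231. Φ(0.00081/0.01231) = Φ(0.07) ≈ 53%.

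Expected patients with a recorded AE (intervention v control) and chance of a false excess:

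| Assumed r | s = 0 | s = 0.25 (ratio 4) | s = 0.5 (ratio 2) | s = 1 (ratio 1) |
|---|---|---|---|---|
| 2% | 9.5 v 0; 87% | 9.5 v 2.4; 55% | 9.5 v 4.7; 24% | 2.5% |
| 5% | 23.7 v 0; 99.9% | 23.7 v 5.9; 91% | 23.7 v 11.9; 53% | 2.5% |
| 10% | 47.4 v 0; about 100% | 47.4 v 11.9; 99.8% | 47.4 v 23.7; 83% | 2.5% |

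The normal approximation is rough where counts are small, and {20b} names no significance test for AEs. The table therefore shows direction and sensitivity to recording. It is not an estimate for this trial.

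**The case against.** Several points on the other side are sound.

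- **A control count of zero is not certain.** A reader might infer that controls must show 0 of 474. The harms section removes a duty; it does not forbid recording. Table 1 makes no distinction by arm, and the assessments named as a detection route take place in both. The supportable statement is that control recording is absent, or voluntary and unequal.
- **Comparative safety information is not wholly lost.** A reader might infer that nothing can be said about relative safety. Unplanned readmissions are the primary outcome, death is collected from insurance data and analysed by Cox regression, and laboratory values are taken from A0 to A3 with shift tables planned. These sources do not, however, supply AE category, relation, severity or intensity.
- **Recorded events are not automatically attributed to eliPfad.** Relation is assessed event by event. That helps with individual cases but does not correct unequal counts.
- **Stopping at T2 is defensible.** It follows the period of exposure to the intervention. The fault is only that Table 1 says otherwise.
- **One-arm documentation is deliberate.** The harms section justifies it by the open-label design. Lack of blinding does not prevent recording in controls, but one-arm documentation would be coherent if no between-arm comparison were promised.
- **The core of the trial is untouched.** AEs are neither the primary outcome nor a listed secondary hypothesis.

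These points limit the consequence and the severity. They do not remove the contradiction between {20b}, {22} and Table 1.

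**Conclusion.** The point holds as an internal contradiction with a predictable direction of bias. The AE comparison promised in {20b} cannot be done validly with data collected under {22}, and attempting it would tend to show a spurious excess with eliPfad. How large that excess would be depends on AE risks and on the share of control events recorded, and the article gives neither. What is lost is a valid between-arm comparison of AEs by category, relation, severity and intensity; deaths, unplanned readmissions and laboratory values remain comparable. Separately, Table 1 and {22} disagree on whether AEs are collected in the last 138 of the 180 post-discharge days.

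Severity: should-fix. The primary outcome, its analysis and the sample size are unaffected.

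**What to change.** Reconcile {20b}, {22} and Table 1 in one of two ways.

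1. **Keep the comparison.** Ask the same AE and SAE questions in both arms at the existing A1 and A2 visits, and at A3 if Table 1 stands. Restrict the between-arm comparison to events elicited at those visits, and report events found through video calls descriptively for the intervention arm. State the remaining limits: weekly contact may make intervention patients more likely to report events at A2, assessors are not blinded ({17a}), and for controls enrolled before the change earlier events are available only by recall.
2. **Drop the comparison.** Delete the clause on treatment comparisons from {20b} and describe AEs in the intervention arm only. Base comparative safety statements on the two-arm data already planned: death, unplanned readmissions and laboratory values. Cause-specific admissions, such as those for falls, should not be promised, because they are not among the insurance variables listed under {12}.

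In either case, state one end of AE collection, T2 or T3, in both {22} and Table 1.

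Cost: the first option means slightly longer control visits, added eCRF items and a protocol amendment; under {25} the ethics committees must deliberate if the change is substantial, and recruitment began on 09/01/2023. The second option needs only a change of wording and no new data collection.

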#### Subgroup analyses

Subgroup analyses are performed by sex, age, index diagnoses as defined in the inclusion criteria section, and study center. There is no alpha adjustment for multiple comparisons.

### Methods in analysis to handle protocol non-adherence and any statistical methods to handle missing data {20c}

The occurrence of missing data is minimized as much as possible through careful study planning and execution. For the primary analysis, all individual times under risk are considered, especially for patients lost to follow-up or dropped out. Moreover, since the primary endpoint data is obtained by health insurance companies, we do not expect a relevant amount of missing data for the number of rehospitalizations. Time-to-event analysis and mixed models deal naturally with missing values. For further analyses, missing data are replaced by multiple imputation if necessary and the results obtained are summarized according to Rubin’s rule [41]. The missing values are first replaced under the missing-at-random (MAR) assumption. In addition, not-missing-at-random (NMAR) scenarios can be realized by post-processing multiple substitutions.

### Plans to give access to the full protocol, participant-level data, and statistical code {31c}

Access to the full protocol, participant data, and statistical code may be granted upon request and approval by the steering committee.

## Oversight and monitoring

### Composition of the coordinating center and trial steering committee {5d}

The University Hospital Cologne represents the coordinating center in this trial. The steering committee comprises representatives from the coordinating center, the figus institute, the Gesundheitsnetz Köln Süd, and the Institute of Health Economics and Clinical Epidemiology (IGKE). The steering committee is responsible for recruitment, intervention development, and evaluation. The steering committee will meet every 2 weeks. Data that will be reviewed are foremost data regarding recruitment/enrollment stratified by the different study centers. The committee ensures that enough p1atients are recruited to reach the planned sample size. Strategies will be discussed on how recruitment can be improved in case numbers are not met.

The participating centers/hospitals are the University Hospital Cologne, University Hospital Aachen, Hospital Dortmund, Hospital Herne, and as one center with two corresponding hospitals the St. Franziskus Stiftung in Münster with St. Franziskus Hospital and Hospital Hiltrup.

Two principal investigators (PIs) represent the coordinating center on the steering committee and are responsible for conducting the study at the University Hospital Cologne. In addition, there is a project coordinator who assists in the implementation of the PIs’ decisions and acts as an interface between all professional groups of the coordinating center. Two study physicians are responsible for the daily implementation of the study at the University Hospital Cologne site. They obtain informed consent from suitable patients, develop the treatment plan together with the case manager, and communicate primarily with the physicians in the outpatient area. Furthermore, a case manager is responsible for the patients at the University Hospital Cologne site. She supports the patients in using the tablet and medical devices, draws up the treatment plan and is the primary contact for patients. She also conducts the weekly video calls with the patient after discharge from the index hospital stay. A study nurse is also employed to carry out the patient assessments, enter the data into the database and check it for completeness. Finally, a study nurse carries out the cross-center monitoring but is not otherwise involved in the implementation of the study. At each of the other centers, 1 study physician, 1 case manager, and 1 study nurse are employed for the tasks described above. The members of each center involved in the day-to-day study activities meet once a day to coordinate the day and assign tasks. Each center has hired its own employees and works independently.

### Composition of the data monitoring committee, its role and reporting structure {21a}

The establishment of an official data monitoring committee (DMC) is not planned. However, to ensure data quality, regular checks will be performed during the study by employees of the coordinating center (risk-based monitoring). The risk-based monitoring will be carried out by the coordinating center. The data entered in the electronic data capture system for randomly selected patients from all centers are examined for completeness (missing data) and implausible values. At least one these monitorings at each study center will be on site. The results of the monitoring are communicated to the centers so that they have the opportunity to supplement missing data or correct implausible values. Regular meetings of the assigned employees of the coordinating center with the documentarists, study nurses, case managers, and physicians of the participating study centers serve to optimize the processes and correct existing deficiencies.

### Adverse event reporting and harms {22}

No adverse events (AEs) in the strict sense are expected to be caused by the intervention. However, due to pre-existing (chronic) diseases, numerous complications are possible. In addition, the participants’ underlying diseases may worsen. These complications are not documented separately.

No novel or unapproved methods will be used as part of the intervention. Conceivably, a safety-related event could occur during independent home exercise; for example, a fall during a mobilization exercise. Events such as these and all other events that are not associated with the natural course of the pre-existing (chronic) diseases are documented as an AE. In case that such an event leads to hospitalization or death of the patient, it will be recorded as an SAE. AEs and SAEs will be recorded in the electronic data capture system (secuTrial® database) by the study team. AEs and SAEs will be identified by the study team during the weekly video calls between the case manager and the patient or during the assessments. SAEs will be immediately reported to the sponsor by the study teams.

Due to the open-label character of the trial, the obligation to document safety-related events begins in the intervention group at the time of enrollment and ends after the 6-week outpatient phase following the index inpatient stay at T2. There is no documentation requirement in the control group.

An overview of safety-relevant events will be provided to the ethics committee upon request after completion of the study.

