Beneficial to their self-management, patients are supported by a “smart assistant,” consisting of a tablet and electronic smart devices, which enable the patients to measure their vital parameters themselves when at home. Monitored vital parameters include blood pressure, pulse, body temperature, body weight, step count, saturation of peripheral oxygen, and, if necessary, blood sugar. Threshold values for these vital parameters are determined for each patient individually in line with evidence-based medical guidelines. The measured vital parameters are transferred to the electronic medical record once daily. Videos of the exercises taught by the physiotherapists during the hospital stay are retrievable on the tablet and allow patients to practice on their own after discharge. Furthermore, the tablet provides the patients with information about their diseases and the corresponding rationales for the specific treatments, the correct frequency and intake of the prescribed drugs, and general information on the importance of healthy nutrition and physical activity. Moreover, the tablet automatically reminds patients of their medication schedule via notification and requests digital confirmation of the intake. Finally, patients are asked to fill in a digital health diary, assessing the development of their subjective well-being, the occurrence and severity of various symptoms, and the level of self-efficacy.

Before patients are discharged from the hospital, the case manager coordinates the seamless continuation of the treatment plan in the ambulatory setting. In the first week after discharge, the case manager visits the patients in their home environment and ensures that all devices work properly. The patients continue their therapeutic exercises at home, supported by the videos on the tablet, and measure their vital parameters daily. The case manager inspects the vital parameters twice weekly and ascertains that none of the predefined thresholds is exceeded. The patient’s subjective well-being is ensured, additionally to the patient’s reported answers from the health diary, through weekly video calls between the case manager and the patient. The main contact person for health and medical-related questions during the period at home is the patient’s GP. Measured vital parameters along with other relevant health care information of each patient are reported once weekly via standardized reporting sheets in the electronic patient file to their GP.

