#### Time frame of the intervention

Patients are enrolled within two working days after admission to an internal ward (see eligibility criteria above) and the hospital part of eliPfad begins. After discharge from the index hospital stay, patients will be treated in eliPfad for 42 days in the ambulatory setting. This time frame is fixed and will not be prolonged due to planned or unplanned hospital stays within the 42 days. Should the patient be admitted to a hospital within 42 days, the intervention would pause during that period and resume afterward—given that the 42nd day after the initial discharge is not yet reached. A follow-up visit is planned 6 months after the discharge from the index hospital stay.

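### The stated SAE rule (hospitalization or death) does not fit the inpatient part of its own safety window, where patients are already in hospital

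*Protocol article*

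**What the plan says.** All the rules that matter here stand in the protocol article under Adverse event reporting and harms {22}.

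- What counts as an AE: besides falls and similar mishaps during home exercise, "all other events that are not associated with the natural course of the pre-existing (chronic) diseases are documented as an AE".
- When an AE becomes serious: "In case that such an event leads to hospitalization or death of the patient, it will be recorded as an SAE". The article states no other seriousness criterion.
- What follows from seriousness: "SAEs will be immediately reported to the sponsor by the study teams". No comparable duty is stated for AEs that are not serious.
- When documentation applies: it "begins in the intervention group at the time of enrollment and ends after the 6-week outpatient phase following the index inpatient stay at T2".
- How events are found: "AEs and SAEs will be identified by the study team during the weekly video calls between the case manager and the patient or during the" (the sentence ends by naming the assessments).

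Under Time frame of the intervention, the start is described as follows: "Patients are enrolled within two working days after admission to an internal ward (see eligibility criteria above) and the hospital part of eliPfad begins". Under Course of the intervention, the physical component is placed in hospital as well as at home: "Videos of the exercises taught by the physiotherapists during the hospital stay are retrievable on the tablet". The section on adherence {11c} also has the physiotherapist teaching individual exercises in hospital.

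**The concern.** The seriousness rule works for a patient at home: an injury either leads to an admission or it does not. The safety window, however, begins while the patient is on a ward. In that phase the hospitalization limb of the rule has little to act on, and death is the only other limb. The population is at high risk by design (MPI of at least 0.34), and the exercises begin in this phase.

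What is at stake is prompt awareness of harm. The article plans no data monitoring committee and no interim analysis, and the ethics committee receives a safety overview only on request after the study ends. The SAE report is therefore the only stated route by which the sponsor learns of a serious event without delay. The primary analysis is not affected.

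**Working it through.** No arithmetic applies. The check sets the rule against each situation that the window covers.

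**Inputs.** The seriousness rule, the reporting duty and the window come from {22}. The place and time of enrollment come from Time frame of the intervention. In-hospital exercises come from Course of the intervention and {11c}. Assessment timing comes from Outcomes {12} and Table 1. The timing of the video calls comes from Course of the intervention and section {5d}.

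**Step 1: is every patient an inpatient when the window opens?** Yes. Enrollment happens on the ward, and patients likely to leave within 2 working days are excluded, so each participant is expected to have an inpatient phase inside the window.

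**Step 2: apply the rule as written.**

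| Event in the window | Does it lead to hospitalization or death? | Recorded as | Immediate report stated? |
|---|---|---|---|
| Injury at home, patient admitted | Yes | SAE | Yes |
| Fatal event, any phase | Yes | SAE | Yes |
| Non-fatal event on the ward, index stay prolonged | Not normally: already an inpatient | AE | No |
| Non-fatal event on the ward, intensive or intermediate care in the same hospital | Not normally: already an inpatient | AE | No |
| Event on the ward, patient moved to another hospital | Arguable | Unclear | Unclear |
| Event on the ward that later causes a readmission | Yes, but only once readmitted | SAE | Yes, late |
| New event during a readmission before T2, stay prolonged | Not normally: already an inpatient | AE | No |
| Event at home, lasting disability, no admission | No | AE | No |

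The intervention pauses during a readmission, but no pause is stated for the documentation duty. The seventh row therefore lies inside the window.

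**Step 3: how would an inpatient event be found?** Two routes are named. The weekly video calls take place after discharge, which leaves the assessments. A0 follows directly on randomization, so it will usually precede the exercises. A1 may take place up to 3 days before planned discharge or up to 3 days after discharge at home. The plan therefore has at most one scheduled AE check in hospital once exercises have begun. If A1 is done at home, the check is retrospective.

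**Result.** The rule separates serious from non-serious events for patients at home who are admitted, and for deaths. For most serious non-fatal events in hospital it does not.

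**The case against.** The strongest reply is that this is a condensed article. A separate study protocol (version 1.1) exists and may hold the usual longer list of seriousness criteria. The rule also says when an event is an SAE without saying that nothing else qualifies. This stands as a limit on certainty. It does not remove the point, because the article states both the rule and the window, and the two do not fit. If the full protocol is wider, the article should match it.

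Second, the harm is not lost. Such an event is still an AE, the section on safety-related analyses assesses AEs by severity, and Table 1 schedules AE evaluation at A0 and A1. An A1 at home can still pick up events from the stay just ended. Case managers also see study patients on the ward, and site teams meet daily, although neither is named as a detection route. This stands, and it limits the consequence to classification and speed of reporting.

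Third, the fall that the article gives as an example is placed in independent exercise at home, where the hospitalization criterion works. It should not be read as a ward fall. The inpatient case rests instead on the general AE definition and the exercises taught in hospital.

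A reader might infer that an inpatient injury can never be an SAE unless fatal, or that it is never reported promptly. The documents do not support either. A later readmission would qualify, as arguably would a move to another hospital, and nothing forbids prompt reporting of an AE.

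**Conclusion.** The point holds in a limited form. As the article states it, the seriousness rule does not fit the inpatient part of the documentation window. A serious non-fatal inpatient event would normally be recorded only as an AE, without the immediate sponsor report stated for SAEs.

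The mismatch concerns all 474 patients planned for the intervention arm, since all are enrolled in hospital. The article gives no rate of such events, so neither the number of misclassified events nor their share of all serious events can be stated.

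The conclusion assumes that the article's wording is the operative rule and that study teams apply it literally. A reader might go further and expect a low SAE count to be taken as evidence that eliPfad is safe to adopt. The documents do not say this. The abstract ties adoption to readmissions, (cost-)effectiveness and treatment burden, and with no safety documentation required in the control group, the SAE count could support no comparison under any definition.

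The wording should be corrected: the change is small, and other prompt safety oversight is thin.

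**What to change.** In {22}, extend the seriousness criteria beyond hospitalization and death to prolongation of an existing hospital stay, life-threatening events and persistent disability. State that they apply to the index stay and to any readmission up to T2. If the full protocol already contains these criteria, bring the article into line with it instead.

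Ask explicitly at A1 about events during the index stay. Where A1 precedes discharge, the first video call can cover the remaining days. Cross-check against data that are already collected by A2: length of the index stay and time in intensive or intermediate care. Ward teams need not become AE reporters for this.

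Cost: a small protocol amendment, which needs ethics committee deliberation if it is classed as substantial, and one seriousness field in the eCRF. Enrollment began on 09/01/2023, so AEs already recorded would have to be reclassified for the SAE count to rest on one definition. That count may rise somewhat. No new visit is needed.
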